## Materials and methods

### Study design

This study will be a case-control study nested into a hospital-based, single-center, observational neonatal cohort. Recruited preterm neonates will be followed over their first 28 days of life. The primary clinical endpoint in this study is a blood culture (BC)-proven LOS. Secondary endpoints are clinical sepsis, NEC, death to clinical and/or BC-proven sepsis or NEC, death to any cause, or discharge from the hospital with or without sequelae.

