### Study population and sample size

The study participants will include inborn and outborn preterm neonates born at 28 + 0 to <34 weeks of GA admitted to the neonatal wards, and their respective mothers who consented to participate after a detailed description of the study has been given by trained study team members. Recruited preterm neonates should have a minimal weight of at least 1000 g and be enrolled within their first week of life. We will exclude infants whose mothers are below 18 years of age, have severe, life-threatening illness at the time of admission, and/or have severe comorbidities or severe congenital malformations. Furthermore, neonates or mothers who ever received probiotic supplements during pregnancy will be excluded from this study.

Sample size calculations considered all study objectives and the one requiring the largest sample size will be the basis to determine recruitment numbers. All eligible preterm neonates admitted to the neonatal unit during the 18-month study period will be recruited and closely followed up for 28 days each.

To answer the primary research question on the hypothesis of preterm neonates developing gut dysbiosis before the onset of sepsis we need to identify preterms with BC-proven sepsis, assess their microbiomes, and compare it with controls (matched for GA, sex, mode of delivery, type of feeding, and previous antibiotic exposure). Assuming a rate of BC-proven sepsis of 10% and 25% missed samples we expect to identify 72–135 bloodstream pathogens (positive BCs) with 54–101 complete sets of stool samples for microbiome analysis within 18 months [7,10]. According to Graspeuntner *et al.,* we then expect gut dysbiosis in 30% of the neonates without and 60% of the children with LOS [19].

Our minimal sample size considerations are based on the proportions of gut dysbiosis in children with and without LOS. Assuming an alpha level of 5% and a power of 80% a minimal study number of 84 children (42 with and 42 without LOS) is needed to reject the null hypothesis that no difference in the proportion of dysbiosis between both cases and controls. Cases are defined as preterm neonates who develop LOS and controls as preterm neonates who do not develop any clinical or culture proven sepsis during the observation period (after 72 hours of life).

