### Definitions of LOS, culture proven sepsis, clinical sepsis and NEC

LOS is defined as a bloodstream infection occurs after 72 hours of life, typically caused by nosocomial or community-acquired pathogens [26]. Culture-proven sepsis is identified when a bacterial or fungal pathogen is isolated from a sterile site, such as blood or cerebrospinal fluid. In contrast, clinical sepsis is diagnosed based on clinical signs and symptoms consistent with sepsis in the absence of a BC [27]. The signs and symptoms of neonatal sepsis range from nonspecific manifestations to hemodynamic collapse, requiring a high index of suspicion for timely diagnosis. This study will uniformly apply the WHO criteria for neonatal sepsis, which offer a standardized approach for identifying sepsis in preterm neonates [28]. LOS will be defined by the following criteria by responsible physicians, at least the presence of two signs as per WHO which includes difficulty feeding, convulsions, lethargy, tachypnoea, severe chest indrawing, hypothermia, hyperthermia, bulging anterior fontanelle and skin or umbilical infection with pus requiring systemic antibiotics for at least five days [28].

Cases will be categorized as culture-proven sepsis and clinical sepsis. Instances of positive BCs without accompanying signs or symptoms will be considered contaminants. Specifically, coagulase-negative staphylococci (CoNS) will be classified as a pathogen only if overt signs and symptoms consistent with sepsis, as defined by WHO criteria, are present; otherwise, CoNS will be regarded as contaminants [29]. To improve diagnostic accuracy where available, C-reactive protein (CRP) levels will be used as a biomarker during suspected sepsis episodes, with elevated levels supporting the presence of an inflammatory response [30].

In this study, NEC is defined and suspected clinically based on the presence of one or more of the most characteristic clinical features including abdominal distension, feeding intolerance, bilious vomiting or gastric aspirate and bloody stools, and if available, complemented by the finding on abdominal imaging of intramural gas, pneumoperitoneum or sentinel bowel loops [31,32].

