### Investigation tools’ validity and reliability of the data

All data collection tools will undergo pre-testing during a pilot phase involving at least ten participants before the full study begins. Before the project launch, the entire unit will be briefed on the study’s aims and objectives to ensure that all staff adhere to uniform procedures and standards of care for the vulnerable populations involved. Research assistants will receive training in Good Clinical Practice (GCP), research ethics, and the proper use of study tools, including the REDCap^®^ data management system, to ensure accurate data collection. Continuous training on hygiene, aseptic techniques for drawing and storing blood culture samples, and infection prevention measures will be conducted to minimize contamination and maximize sample yield. Data quality will be regularly monitored by the PIs, study managers, and data managers through reports, data exports, and statistical checks to maintain consistency. All data entries will be cross-checked by another study team member and validated by the study coordinator. A robust data management system led by experienced data managers and the research team will be used to clean and export data for analysis in R statistical software, ensuring the accuracy and integrity of the collected data.

Data entry will be performed by authorized research staff using touch-screen tablets equipped with the REDCap^®^ data management system to allow real-time data entry. Additionally, a customized Android application for the tablets will be utilized locally to manage participant registration, appointment schedules, and sample storage. Entered data will be securely transmitted to servers located at MUHAS and the German site. These main servers will only be accessible to the data managers and PIs on request.

For data validation and resolution, the data management team will conduct monthly reviews using established quality checks to identify discrepancies, missing fields, or logic errors in the collected data. Any issues found will be communicated to the research team for resolution. An automated audit trail will track all corrections, ensuring transparency and accountability throughout the data management process.

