### Statistical analysis

Descriptive statistics will be used to summarize the demographic and clinical characteristics of the study population, including gestational age, birth weight, gender, mode of delivery, and presence of comorbidities. Mean and standard deviation or median and interquartile range for continuous variables will be used and for categorical data frequencies or proportions will be described.

To answer the first objective on the incidence and risk factors of LOS, the incidence density will be calculated as the number of new cases of LOS divided by the total person-time at risk in the cohort. The person-time at risk will be calculated by summing the individual follow-up durations until the occurrence of BC-proven LOS (clinical sepsis, NEC, and death).

Cox-proportional hazard regression will be utilized to investigate the relationship between the risk factors and risk to develop primary and secondary endpoints. First, we will perform univariate cox-regressions for potential risk factors to identify individual risk factors, all variables considered relevant for the study question will be included in the multivariate cox-regression to adjusting for potential confounders. The hazard ratios (HRs) with the 95% confidence intervals (CIs) will be estimated for each risk factor. Etiological agents of LOS/NEC and the respective AMR patterns will be described as the proportion of isolates resistant to each antibiotic and according to international standard.

Microbiome analysis will be performed to evaluate gut dysbiosis in preterm infants prior to the development of LOS and in relation to the microbiome of the mother. Association of relative abundances of microbial species with the factors of gestational age, days of life, diet, and LOS will be limited to species that were found with a non-zero relative abundance in at least 40 stool metagenomes. Square root-transformed relative abundancies will be used and analysed using linear mixed effect (LME) models, where repeatedly collected microbiome data from each child is considered to cluster.

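### Neither the control matching nor the microbiome model includes calendar time, so unit-wide changes over 18 months can look like gut markers that precede LOS

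*Protocol article*

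**What the plan says.** The Study design section sets up a "case-control study nested into a hospital-based, single-center, observational neonatal cohort". Accrual lasts 18 months: "All eligible preterm neonates admitted to the neonatal unit during the 18-month study period will be recruited" (Study population and sample size). The same section says controls are "matched for GA, sex, mode of delivery, type of feeding, and previous antibiotic exposure" and defines "controls as preterm neonates who do not develop any clinical or culture proven sepsis during the observation period". It sets no limit on when a control was admitted relative to its case, and describes no concurrent or risk-set sampling.

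Under Statistical analysis, the mixed model relates the relative abundance of each species "with the factors of gestational age, days of life, diet, and LOS", with repeated samples clustered by child. Days of life is postnatal age, not calendar time. Table 1 lists no date, season or study-period variable among the candidate predictors.

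Three other statements bear on this:
- The definitions section describes LOS as "typically caused by nosocomial or community-acquired pathogens".
- The sample-size section says the rate of positive cultures varies with diagnostic quality and with the blood volume drawn.
- The section on validity and reliability says: "Continuous training on hygiene, aseptic techniques for drawing and storing blood culture samples, and infection prevention measures will be conducted".

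**The concern.** The primary research question is about the infant: does dysbiosis precede LOS, and do markers identify which infants are at high risk? In a single unit, infants admitted together share staff, equipment and circulating strains. Calendar time can therefore influence three things at once: the risk of nosocomial LOS, the chance that LOS is confirmed by culture, and the flora an infant acquires.

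If the first or second varies together with the third, cases come disproportionately from certain periods while controls may come from all 18 months. A species that was simply common in the unit in those periods will then differ between cases and controls. The child-level clustering does not remove this, because admission date and LOS status both vary between children, not within them. The analysis could then return a marker of when an infant was admitted rather than of which infant was at risk.

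**Working it through.** **The plan's own figures.** With 30% v 60% dysbiosis, two-sided 5% and 80% power, the pooled-variance formula gives [1.96 × √(2 × 0.45 × 0.55) + 0.842 × √(0.21 + 0.24)]² / 0.30² = 41.97, so 42 per group and 84 in all, as stated. (Unpooled variance gives 40.) The expected counts also reproduce: 720–1350 × 10% = 72–135 cases, and × 75% = 54–101 with complete stool sets. Nothing below changes these figures.

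**Illustration 1: carriage of one species.** All inputs are assumed, because the documents give none. A high-LOS period covers 3 of 18 months, and carriage outside it is 15% in all infants. Within a period, carriage is unrelated to LOS.
- Cases: s × q + (1 − s) × 0.15, where s is the share of cases in the high period and q is carriage in it.
- Controls: (3/18) × q + (15/18) × 0.15.
- Implied LOS risk ratio, high v other months: (s/3) / ((1 − s)/15).
- Rejection at two-sided 5%: Φ(d/SE − 1.96) + Φ(−d/SE − 1.96), where d is the difference and SE² = pc(1 − pc)/n1 + pn(1 − pn)/n2 (pc cases, pn controls).

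| s | q | Implied LOS risk ratio | Cases | Controls | OR | Reject, 54 v 54 | Reject, 101 v 202 |
|---|---|---|---|---|---|---|---|
| 20% | 50% | 1.25 | 22.0% | 20.8% | 1.07 | 5% | 6% |
| 25% | 40% | 1.7 | 21.3% | 19.2% | 1.14 | 6% | 7% |
| 30% | 50% | 2.1 | 25.5% | 20.8% | 1.30 | 9% | 15% |
| 40% | 60% | 3.3 | 33.0% | 22.5% | 1.70 | 23% | 48% |

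Last row at 54 v 54: SE = √((0.2211 + 0.1744)/54) = 0.0856; d/SE = 0.105/0.0856 = 1.23; Φ(−0.73) + Φ(−3.19) = 0.23. The 1:2 ratio in the last column is also assumed, since the article says only that more controls than the minimum are intended. Taking the cases out of the control pool (10% LOS) raises the last two odds ratios to 1.34 and 1.82.

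**Illustration 2: a common marker.** Also assumed: overall LOS 10%; a high period covering f = 1/6 to 1/2 of recruitment; LOS risk in it RR = 1.5 to 3 times higher; marker prevalence 30% outside it and 50–80% inside. LOS risk outside the period is r0 = 0.10/(1 − f + f × RR). The share of cases in the period is f × r0 × RR/0.10, and of controls f × (1 − r0 × RR)/0.90.
- Middle case (f = 1/3, RR = 2, 60% inside): r0 = 0.075; share of cases 0.50, of controls 0.315; prevalence 0.30 + 0.30 × 0.50 = 45.0% v 0.30 + 0.30 × 0.315 = 39.4%; OR 1.26.
- Whole grid: difference 1.4 to 14.8 points; OR 1.07 to 1.82.
- Chance of a significant result in that direction (nominal 2.5%): 3–27% at 42 per group (middle 7%) and 4–56% at 101 per group (middle 12%).

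In both illustrations, comparing within calendar period makes the spurious difference zero, by construction.

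**Room for date matching.** If 25% of samples are also missed in infants without LOS, the sampled pool is at most 720–1350 × 0.9 × 0.75 = 486–911, or 27–51 a month and 81–152 a quarter, before infants with clinical sepsis are removed. A window of ±30 days is about 2 of 18 months, one ninth of the pool: 54–101. The five existing factors can already form about 6 gestational weeks × 2 sexes × 2 delivery modes × 5 feeding categories × 2 antibiotic states = 240 cells.

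**The case against.** The strongest reply is that none of this is documented as happening. A reader might infer that outbreaks will occur, that cases will bunch in some months, or that the study itself alters infection control as it proceeds. The article supports none of these as fact. It reports no outbreak, season or clustering, and the continuing training can be read as upkeep of one standard, since a pre-launch briefing aims at uniform procedures. This stands: the bias is a risk that needs LOS (or its detection) and flora to vary together.

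Other points that stand, in whole or part:
- **The size depends on the inputs.** Mild inputs give almost no inflation. The illustrations also use an unmatched test of a binary marker, whereas the plan models square-root abundance in a mixed model.
- **The Cox models are not at fault on the text.** A reader might infer that they too exclude calendar time. But "all variables considered relevant for the study question will be included in the multivariate cox-regression" leaves room for admission date. That clause does not cover the microbiome comparison.
- **An outbreak strain may be a true precursor.** The introduction cites agreement between blood and gut isolates. Comparing within periods sets aside the between-period part of the association; it does not show that part to be false.
- **The article is condensed.** The full protocol or an analysis plan may add a calendar term. The matching factors and the model's named factors are nevertheless stated here, and neither list has one.

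**Conclusion.** The point holds as a risk worth removing, not as a demonstrated bias. On the text, calendar time is absent from both the matching list and the factors named for the microbiome model, in a single-unit study of 18 months whose own statements give a plausible route for LOS risk, culture yield and flora to shift together.

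The size cannot be known from the documents. Under the assumed inputs it runs from an odds ratio of about 1.1 with rejection near 5% to an odds ratio of about 1.7 to 1.8 with rejection several times nominal. The exposure lies mainly in the species-level tests, where modest differences would be reported. A reader might infer that the sized comparison is undermined as well. It is not on these figures: the largest spurious difference is 14.8 points, against the 30 points for which the study is sized, and the minimum of 42 per group is unaffected.

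**What to change.** 1. Add calendar time of admission to the microbiome mixed model: a random effect for month or quarter, or a spline. With only six quarters, fixed quarter effects or a spline adjust more fully, because a random effect is shrunk and can leave part of the between-period difference in place.
2. Choose controls from the same broad calendar period, for example the same quarter, where the existing matching factors allow. Where they do not, rely on the model term.
3. Report LOS counts and the main species by month, so that readers can see whether the two moved together.
4. Give the calendar-adjusted and unadjusted estimates side by side.

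**Cost.** No new data should be needed, since admission dates come with recruitment. The model term uses a few degrees of freedom (five for six quarters). Date matching does cost controls: a quarter keeps about one sixth of the pool, and a ±30-day window about one ninth, on top of five factors. A tight window could leave cases unmatched, so the model term should be the main remedy. The adjusted estimate describes within-period association only, which is why the unadjusted one should stay beside it.

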### Research questions

Our primary research question aims to answer whether gut dysbiosis precedes the development of LOS and/or NEC in Tanzanian preterm neonates and whether microbial or metabolomic markers predict neonates at high risk. Secondary research questions include 1) What are the maternal and neonatal risk factors for LOS and/or NEC? 2) What are factors associated with disease severity and outcomes? 3) What bacteria species and AMR profiles are found in blood culture isolates of preterm neonates with LOS and/or NEC?

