The calculations are based on formulae 1 for a two-sample proportions test, where *n*_*i*_ is the sample size estimated for each group, z is the normal deviation defined for the alpha level (α) and the study power (β), and *p*_*i*_ is the proportions in the respective groups.

$$n_{i}=\frac{{\left(Z\alpha /2+Z1-\beta \right)}^{2}*(p1(1-p1))+(p2(1-p2))}{{\left(p1-p2\right)}^{2}}$$
(formulae 1)

These parameters define minimal study numbers to reach power and significance. We aim to include all cases of LOS and NEC with complete microbiome and a higher number of controls, to improve the statistical power of the study, precision of the applied data analysis and allow potential subgroup analyses [19].

In the literature, the rate of positive BCs varies between study sites and is highly dependent on the quality of diagnostic procedures as well as the amount of blood transferred into BC bottles. Based on the available data and our experiences we are expecting to screen 80–100 admissions per month in the respective GA range and a study inclusion rate of 50–75%. Thus, we expect to recruit approximately 40–75 admitted newborns per month for a period of 18 months, which amounts to 720–1350 admissions over the study period. The calculations were enforced by comparing data from previous studies [7,24] and the ongoing NEST360 survey in the NCU [25], powered to identify sepsis incidence, risk factors, and mortality rates of LOS and NEC among preterm neonates.

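### The 80% power belongs to a comparison of dysbiosis proportions and does not carry over to the species-abundance mixed models that the analysis section specifies

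*Protocol article*

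**What the plan says.** The section Study population and sample size ties the size of the microbiome comparison to a yes/no state of each child: "Our minimal sample size considerations are based on the proportions of gut dysbiosis in children with and without LOS". The assumed contrast is "we then expect gut dysbiosis in 30% of the neonates without and 60% of the children with LOS". The requirement reads "Assuming an alpha level of 5% and a power of 80% a minimal study number of 84 children (42 with and 42 without LOS", for a null hypothesis of equal dysbiosis proportions in cases and controls. The test is named as well: "The calculations are based on formulae 1 for a two-sample proportions test". The same section matches controls to cases on five factors: gestational age, sex, mode of delivery, feeding type and earlier antibiotic exposure. It expects 54 to 101 cases with complete stool sets and intends to use more controls than the minimum.

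The section Statistical analysis says in general terms that dysbiosis before LOS will be evaluated. It then specifies one microbiome model. Species abundances are related to gestational age, days of life, diet and LOS, for species detected in at least 40 stool metagenomes. "Square root-transformed relative abundancies will be used and analysed using linear mixed effect (LME) models", with repeated samples clustered by child. Samples taken after LOS diagnosis are dropped, and the R package is named.

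**The concern.** The two sections describe different analyses of the same question. One has a single binary outcome per child, two groups and one test. The other has a continuous outcome per sample, repeated within child, for each species that passes the filter. The Cox models in the same section relate risk factors to clinical endpoints, so they do not test the dysbiosis proportion either. The matched sets do not reappear in the analysis. Gestational age and diet return as model factors, but the matching as such is not used.

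If the analysis section is followed as written, the 5% and 80% that justify the sample size belong to a test it does not list. The tests it does list have no stated power and no stated overall error rate. It would then be unclear which result answers the primary question, and what counts as dysbiosis could be settled after the species results are known.

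**Working it through.** **Inputs.** From Study population and sample size: proportions 0.30 and 0.60, alpha 5%, power 80%, 1:1 groups for the minimum, and 54 to 101 expected complete case sets. Formula 1 uses Z at alpha/2, so the test is two-sided. Normal quantiles are 1.96 and 0.8416, and (1.96 + 0.8416)² = 7.849.

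1. **The plan's own figure, pooled variance.** The mean proportion is 0.45, so 2 × 0.45 × 0.55 = 0.495 under the null. Under the alternative, 0.6 × 0.4 + 0.3 × 0.7 = 0.45. Then n = (1.96 × √0.495 + 0.8416 × √0.45)² / 0.30² = (1.379 + 0.565)² / 0.09 = 41.97, so 42 per group and 84 in all. Power at 42 per group is 80.0%. The figure reproduces.

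2. **Same test at the expected numbers.** With equal controls, power is 89% at 54 per group and 99% at 101 per group.

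3. **Formula 1 as printed.** The brackets let the squared quantile term multiply only p1(1 − p1), so the result depends on which group is p1, which the article does not say.
   - p1 = 0.30: (7.849 × 0.21 + 0.24) / 0.09 = 20.98, so 21.
   - p1 = 0.60: (7.849 × 0.24 + 0.21) / 0.09 = 23.26, so 24.
   - Brackets corrected: 7.849 × 0.45 / 0.09 = 39.2, so 40.
   
   None of these is 42. Of these versions, only the pooled one in step 1 gives 42.

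4. **Species models.** Power here would need a species-level effect, its standard deviation, the within-child correlation, the number of species retained and a multiplicity rule. The article gives none of these, so no power figure can be derived. The expected number of false positives can be illustrated. For the LOS term, with every null true and each test at 5%, it is 0.05 × 50 = 2.5 for 50 species and 0.05 × 200 = 10 for 200. The species counts are assumptions.

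5. **A matched version of the powered comparison.** Take 1:1 pairs with no within-pair correlation (assumption). The discordant probabilities are 0.6 × 0.7 = 0.42 and 0.4 × 0.3 = 0.12, with sum 0.54 and difference 0.30. The McNemar calculation gives n = (1.96 × √0.54 + 0.8416 × √(0.54 − 0.09))² / 0.09 = (1.440 + 0.565)² / 0.09 = 44.7, so 45 pairs. At 42 pairs, (0.30 × √42 − 1.440) / 0.671 = 0.75, which is 77% power. The 84-child statement therefore cannot simply be moved to a matched analysis. Within-pair correlation or more controls per case would change the 45.

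**The case against.** The strongest reply is that the article does name the comparison. The sample-size section states the null hypothesis, the groups, the matching factors and the test. The abstract repeats the comparison with matched controls, and the analysis section says dysbiosis will be evaluated. This is a condensed article and its statistical analysis plan is not shown. A per-child dysbiosis rule, a matched-set model and a multiplicity rule are all things such a plan commonly holds. The bracket slip may be typesetting and changes nothing in the conduct of the study.

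Much of this stands. A reader might infer that the dysbiosis hypothesis will never be tested, or that the primary question has no confirmatory answer. The documents do not support that, because the test is named, though in the sample-size section. The absence of a dysbiosis rule or a multiplicity rule from the article is also not a fault in itself.

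The reply does not remove the mismatch. The analysis section is not silent about the microbiome. It fixes the outcome, transformation, prevalence filter, model and software, and what it fixes is not the test that was powered. An analysis plan that followed it would inherit the discrepancy between two printed sections.

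**Conclusion.** The point holds in this form: the 80% power and the 42 + 42 children apply only to a two-sample comparison of dysbiosis proportions, and they do not carry over to the species-level mixed models that the analysis section specifies. For the comparison that was powered, the size is sound and the expected 54 to 101 cases would give 89% to 99%.

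Two stronger readings are tempting and should be resisted.
- **That the study is underpowered.** A low power figure for the species tests would need an assumed species count, an assumed strict adjustment and a 30%/60% contrast that these models do not contain. More cases, more controls and repeated samples could all help.
- **That the 84 is wrong because formula 1 does not return it.** The figure is right for the pooled test, and the printed formula is what needs correcting.

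The 2.5 to 10 false positives rest on 50 to 200 retained species, all nulls true and no adjustment. Reading the models as one per species is natural, but the article does not spell it out. The primary question's wording on "whether microbial or metabolomic markers predict neonates at high risk" raises a separate, minor matter and is not part of this point.

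**What to change.** - In Statistical analysis, name one primary microbiome analysis: the case-control comparison of a per-child dysbiosis indicator. Define the indicator from samples taken before LOS, and from time-matched samples in controls, and lock it before sequence data are linked to case status. Use a method that respects the matching, for example conditional logistic regression, at two-sided 5%.
- Restate the minimum size for that matched analysis with its assumptions. At 1:1 and no within-pair correlation it is about 45 pairs. The expected 54 to 101 case sets cover this, provided each has a usable sample before LOS and a matched control.
- Make the species-level mixed models secondary, with Benjamini-Hochberg control of the false discovery rate.
- If the two-sample calculation is kept, replace formula 1 with the pooled-variance version that yields 42, and say which group is p1.

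The cost is wording in the protocol and analysis plan, with no new data or samples. The downside is that fewer species-level claims will be possible.

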### Samples collection

#### Blood cultures.

To describe the etiological agents and AMR patterns of neonatal bloodstream infections, we will be collecting 1–2 ml sterile blood for cultures [35] in BD BACTEC™ Peds Plus BC bottles according to international recommendation guidelines in all participants developing signs and symptoms of LOS or NEC [36], without delaying antimicrobial treatment. For participants at risk of developing early onset sepsis (EOS), termed as presumed EOS according to standard treatment guidelines, and started on antibiotics based on risk factors, BCs will also be taken free of charge before initiation of treatment whenever possible. Another BC will be taken in cases of switching, adding, or escalating antibiotic therapy. An episode of sepsis will be classified as culture-proven sepsis or clinical sepsis depending on BC results and additional clinical information by the study physicians. The blood culture samples will be processed in the microbiology laboratory at MNH which is certified in accordance with the international standard (ISO 15189:2022).

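### Controls are not barred for NEC, and the primary case group is defined in several ways, so group membership is not fixed and the dysbiosis contrast can be diluted

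*Protocol article*

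**What the plan says.** All places are in the protocol article.

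**Controls.** The section Study population and sample size defines "controls as preterm neonates who do not develop any clinical or culture proven sepsis during the observation period", counted after 72 hours of life. Sepsis is the only disease named.

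**NEC.** Research questions makes dysbiosis before LOS and/or NEC the primary question. Study design lists NEC as a secondary endpoint, separate from sepsis. The sample size section states: "We aim to include all cases of LOS and NEC with complete microbiome and a higher number of controls". The definitions section recognises NEC "based on the presence of one or more of the most characteristic clinical features including abdominal distension, feeding intolerance" and other abdominal signs, with imaging where available. It does not require a sign of sepsis.

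**Cases.** Study design takes culture-proven LOS as the primary endpoint, and the sample size section builds its expected case count on culture-proven sepsis. The same section then calls any infant who develops LOS a case. The definitions section describes LOS once as a bloodstream infection and once as at least two WHO signs, and it divides cases into culture-proven and clinical sepsis.

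**Clinical sepsis.** The definitions section says "clinical sepsis is diagnosed based on clinical signs and symptoms consistent with sepsis in the absence of a BC". The Blood cultures section says: "An episode of sepsis will be classified as culture-proven sepsis or clinical sepsis depending on BC results and additional clinical information".

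**Size.** The plan states "we then expect gut dysbiosis in 30% of the neonates without and 60% of the children with LOS", and from this: "Assuming an alpha level of 5% and a power of 80% a minimal study number of 84 children (42 with and 42 without LOS").

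**The concern.** In a nested case-control study the two group definitions are the design. Here one kind of infant, with NEC and no sepsis, satisfies the control rule and also belongs to a disease group that the plan wants to compare with controls. If dysbiosis precedes NEC, each such infant in the control group raises control dysbiosis and shrinks the contrast.

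The case side is open as well. Two analysts working from this text could build different primary case groups, one of culture-proven infections only and one that adds clinical sepsis or NEC. The sample size rests on the first. If the choice were made after the sequencing data had been seen, it would be post hoc.

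**Working it through.** **1. Where each infant falls**

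| Infant (after 72 hours) | Control rule | Case side |
|---|---|---|
| Culture-proven LOS | excluded | case under every definition |
| NEC that also meets the sepsis criteria | excluded | case, as sepsis or NEC |
| NEC, sepsis criteria not met | **eligible** | **case** under the aim to include all LOS and NEC cases |
| Two WHO signs, culture negative | excluded under Blood cultures; not excluded under the literal clinical-sepsis definition | case under the two-sign rule; not a case if cases are culture-proven only |

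The third row is a direct conflict. The fourth is a wording conflict: the definitions section ties clinical sepsis to having no culture, while Blood cultures has a culture drawn in all participants with signs of LOS or NEC and classifies the episode by its result.

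**2. Which case definition the numbers use**

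Expected cases: 10% of 720-1350 recruits = 72-135. With 25% missed samples, 0.75 × 72 = 54 and 0.75 × 135 = 101. These are the plan's figures, and they count positive cultures only. Clinical sepsis and NEC are not in them.

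**3. The plan's sample size**

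Inputs: p0 = 0.30, p1 = 0.60, two-sided alpha 0.05 (z = 1.960), power 0.80 (z = 0.842), equal groups. With the pooled-variance formula for two proportions and p̄ = 0.45:

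n = [1.960·√(2·p̄(1−p̄)) + 0.842·√(p0(1−p0) + p1(1−p1))]² / (p1−p0)²
= (1.379 + 0.565)² / 0.30² = 41.97, so **42 per group**. Power at 42 is 80.0%.

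The stated 84 reproduces. The unpooled form, which the printed formula appears to intend, gives 39.2, so 40 per group. The brackets exactly as printed would give about 21, which looks typographical and does not matter here.

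**4. Illustration of dilution**

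Two assumptions are needed because the documents give neither figure: a share f of controls are misplaced infants, and their dysbiosis rate is 60%, as in cases. Then control dysbiosis = 0.30 + f × (0.60 − 0.30).

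| f | Control dysbiosis | Difference from 60% | n per group for 80% | Power, 42 per group | Power, 54 per group | Power, 101 per group |
|---|---|---|---|---|---|---|
| 0 | 30% | 30 points | 42 | 80.0% | 89.1% | 99.3% |
| 5% | 31.5% | 28.5 points | 47 | 75.5% | 85.5% | 98.6% |
| 10% | 33% | 27 points | 53 | 70.6% | 81.2% | 97.5% |
| 20% | 36% | 24 points | 67 | 59.8% | 71.0% | 93.3% |

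The columns for 54 and 101 take the expected complete case sets with one control each. The third column does not depend on sample size: more infants raise power, but the estimated difference stays too small.

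**The case against.** **The intent is clear enough.** Study design names culture-proven LOS as primary and NEC as secondary. Setting NEC cases against controls suggests that NEC infants were not meant to be controls, and the aim to include all LOS and NEC cases does not say that the two are pooled. This stands as a reading of intent. It does not alter the control rule, which names sepsis only and would be applied as written.

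**Culture-negative sepsis.** A reader might infer that infants with signs and a negative culture will be used as controls. The documents do not support that. The control rule bars clinical sepsis, the two-sign criterion for LOS requires no culture result, and Blood cultures treats every sepsis episode as culture-proven or clinical. The phrase about the absence of a culture may be a slip for the absence of a positive one. It needs reconciling and is not a rule that admits such infants.

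**Overlap of NEC and LOS.** A reader might also infer that the two cannot be told apart, because feeding problems appear on both lists. LOS needs two signs, and abdominal distension, bilious vomiting or aspirate, and bloody stools are not on its list. NEC infants who do meet the sepsis criteria are already barred from controls.

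**Power.** The minimum of 42 per group is the least favourable case. The plan expects 54-101 complete case sets and more controls than cases. With 54 cases and 108 controls (a 2:1 ratio is assumed), power is 91% at 10% misplaced and 83% at 20%. This stands for power. It does not answer the bias.

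**Conclusion.** The point holds for NEC in the control group and for the unsettled primary case definition. An infant with NEC who does not meet the sepsis criteria is eligible as a control, and under the study's own hypothesis this biases the dysbiosis comparison toward no difference. Had such infants the same 30% rate as other controls, there would be no dilution, so the direction rests on that hypothesis.

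The size is illustrative. With 5-20% of controls misplaced at 60% dysbiosis, power at 42 per group falls from 80% to 75.5-60%. With 10-20% misplaced it is 81-71% at 54 per group and 97.5-93% at 101. The stated sample size is not wrong. The conflict over clinical sepsis is one of wording.

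**What to change.** Settle the following before infants are assigned to groups for the microbiome comparison:

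- **Controls.** Exclude infants with NEC, suspected or confirmed as the article already defines it, as well as any clinical or culture-proven sepsis, over the observation period already stated.
- **Cases.** Use culture-proven LOS, the primary endpoint in Study design, as the single primary case definition. Analyse clinical sepsis and NEC as separate secondary case groups.
- **Wording.** Reconcile the LOS and clinical-sepsis definitions with Blood cultures. For group assignment, an infant who meets the sepsis criteria with a negative or untaken culture counts as clinical sepsis and not as a control.

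No change to the diagnostic criteria for NEC is proposed. The signs of LOS and NEC and the culture results are already recorded, so the cost is text and somewhat fewer eligible controls. Before clinical sepsis and NEC are removed, the expected pool is 720 − 72 = 648 to 1350 − 135 = 1215 infants. The documents do not say how many the exclusions would remove.
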